### Analysis

#### Main analysis

Primary analysis will be intention to treat and will compare HbA1c between the two groups at the 24 month follow-up time point using ANCOVA. Baseline HbA1c will be included as a covariate. These analyses will be corrected for any clustering of outcomes within a clinic. Secondary outcomes analyses will compare the two groups using repeated measures ANOVA. These analyses will also be corrected for any clustering of outcomes within a clinic and baseline levels. Secondary analysis of the primary outcome using repeated measures ANOVA will be carried out using the 3, 12 and 24 month HbA1c values for the two groups and will also involve a more detailed exploratory analysis of the impact of clinic level factors on HbA1c outcome using a two level linear multi-level regression model.

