### Design

This is a multi-centre randomised controlled trial, for children aged 0-17 years who have been newly diagnosed with type 1 diabetes and their parents. Participants will be randomised to receive either hospital management (minimum of 3 overnight stays in hospital) or home management (no overnight stays in hospital).

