### Inclusion and exclusion criteria

Participants will only be entered into the trial if they meet the following inclusion and exclusion criteria (see Table 1)

**Table 1 T1:** Participant inclusion/exclusion criteria

Inclusion criteria (Children)	Exclusion criteria (Children)
1. Children aged 0 - 17 years old	1. Children with ketoacidosis at presentation requiring treatment with intravenous insulin and fluids

2. Newly diagnosed type 1 diabetes (using recognised standard diagnostic criteria) who are clinically well at presentation	2. Children with a co-existing chronic disorder (e.g. cystic fibrosis) which will impact significantly on blood glucose control

3. Written informed consent given by child and assent from child	3. Children with Type 2 diabetes

4. Able to fill out study material (children aged ≥8 years old	4. Children with Maturity Onset Diabetes of the Young (MODY)

5. Written informed consent by parent(s)/carer	5. Children with an uncertain diagnosis

6. Parent/carer able to fill out study material	6. Children who are under the care of the local authority

	7. Children whose home circumstances are assessed as being unsuitable for home management

	8. Children who require hospitalisation for reasons other than their diagnosis

	9. Children who have a sibling with existing Type 1 diabetes

	10. Children who will begin treatment on a Continuous Subcutaneous Insulin Infusion (CSII)

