### Randomisation

Once informed consent/assent is obtained, patients will be remotely randomised using an automated telephone system operational 24 hours a day. Patients will be randomised to either 'Home Management' or 'Hospital Management'.

Randomisation will be stratified by centre and balanced using randomly chosen permuted blocks. The randomisation ratio is 1:1

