### Sample size

In order for a randomised trial to have 80% power to detect an effect size of 0.4 (difference in mean HbA1c of 0.5% with an SD of 1.3% [7]) at a 5% significance level, a total of 200 patients would be required. To allow for loss to follow up of 17%, it is aimed to recruit 240 children. A previous study in Canada which evaluated reducing the amount of in-patient time at diagnosis showed a difference of 0.7% in mean HbA1c at two years[8]. Loss to follow up for the primary outcome of HbA1c should be small, as all of these patients will be attending clinic on a regular basis where HbA1c is monitored for clinical purposes.

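### The primary ANCOVA names baseline HbA1c as its only patient-level covariate; pre-specifying age at diagnosis as well would be a nearly free, optional gain in precision

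*Protocol article*

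**What the plan says.** Under Main analysis, the protocol article says that the intention-to-treat primary analysis "will compare HbA1c between the two groups at the 24 month follow-up time point using ANCOVA". It names one patient-level covariate: "Baseline HbA1c will be included as a covariate". It then adds a centre-level adjustment: "These analyses will be corrected for any clustering of outcomes within a clinic".

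Under Randomisation: "Randomisation will be stratified by centre and balanced using randomly chosen permuted blocks", with equal allocation. Age is not a stratum.

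Table 1 admits "Children aged 0 - 17 years old", and the Design section gives the same range. Eligibility depends on age, so it is known for every child at entry.

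The Sample size section aims for "80% power to detect an effect size of 0.4", described as a mean difference of 0.5% with an SD of 1.3%. It gives 200 evaluable children, raised to 240 for 17% loss to follow-up. The calculation mentions no gain from any covariate.

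**The concern.** The population runs from infants, whose diabetes is managed by their parents, to adolescents who may manage much of it themselves. The article itself treats children differently by age: only those aged 8 or over must be able to complete study material, questionnaires are matched to age, and self-care activity is recorded. It is therefore plausible that age bears on glycaemic control two years on. The one named covariate is measured at diagnosis, before care under either arm begins, and may be only loosely related to control at 24 months. The article does not say how strongly either variable predicts the outcome.

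If age is prognostic, putting it in the model narrows the confidence interval. It also removes the part of the observed difference that comes from a chance difference in age between the arms. Timing matters: if an age imbalance appears and age is added only after the data have been seen, the adjustment is open to challenge. Naming it beforehand avoids that.

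**Working it through.** **Inputs from the Sample size section.** Difference 0.5%, SD 1.3%, stated effect size 0.4, significance level 5% (taken as two-sided), power 80%, 200 evaluable children (100 per arm), 17% loss, 240 recruited.

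**Step 1: reproduce the plan's figure.** Number per arm = 2 × (1.96 + 0.84)² / d².
- With d = 0.4 this gives 99 per arm, or 198 in total, in line with 200.
- 200 / (1 − 0.17) = 241, in line with 240.
- Power at 100 per arm and d = 0.4 is 80.4% by the t-test (80.7% by the normal approximation).

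The plan's figure is reproduced without any age adjustment.

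**Step 2: power on the unrounded inputs.** 0.5 / 1.3 = 0.385. This needs 107 per arm by the normal approximation, or 214 in total. At 100 per arm, power is 77.2% (t-test; 77.6% by the normal approximation). The gap to 80% comes from rounding 0.385 up to 0.4. It is a separate matter and is not caused by leaving age out.

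**Step 3: effect of adding age.** Let R² be the share of variance in 24-month HbA1c that age explains after baseline HbA1c. The document gives no value, so 0 to 0.15 is an assumed range. The 1.3% is taken as the SD before age is added. Then
- residual SD = 1.3 × √(1 − R²);
- effective effect size = 0.385 / √(1 − R²), with power from the two-sample t-test at 100 per arm.

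**Step 4: chance imbalance.** The standardised age difference between arms has SD √(2/100) = 0.141, so its 1.96 SD limit is 0.277. If age is not in the model, the estimate at that limit is shifted by √R² × 1.3 × 0.277.

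| Assumed R² for age | Effective effect size | Power, 100 per arm | Shift at the 1.96 SD imbalance (HbA1c points) |
|---|---|---|---|
| 0 | 0.385 | 77.2% | 0 |
| 0.02 | 0.389 | 78.1% | 0.05 |
| 0.05 | 0.395 | 79.3% | 0.08 |
| 0.10 | 0.405 | 81.4% | 0.11 |
| 0.15 | 0.417 | 83.5% | 0.14 |

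An R² of about 0.07 (a correlation of about √0.07 = 0.26) would bring power to 80% on the unrounded inputs. Starting from the stated effect size of 0.4, the same range of R² takes power from 80.4% to 86.3%. The shifts compare with a target difference of 0.5.

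**Step 5: cost if age is not prognostic.** With 200 children, two arms, eight centres and one baseline covariate, about 200 − 1 − 1 − 7 − 1 = 190 residual degrees of freedom remain if centre is fitted as a fixed effect. A linear age term uses one of these, and a linear plus quadratic form uses two.

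**The case against.** The strongest objection is that the article is a condensed account. It does not say that the covariate list is closed, and a full protocol or analysis plan, not shown here, may already include age. That stands, and it makes the recommendation conditional. The article does, however, choose to state the primary model and its covariate, and the point addresses that stated model.

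Other objections also stand and limit the claim:

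- No part of the article says that age predicts 24-month HbA1c. If it does not, given baseline, nothing is gained. At R² of 0.05 or less the gain is about two percentage points or less.
- A reader might infer that the analysis adjusts for baseline HbA1c and nothing else. The documents do not support that: the same paragraph corrects for clustering within clinic, and centre is the stratification factor.
- A reader might infer that omitting age biases the comparison or inflates the type I error. It does neither. Under randomisation the standard error already allows for chance imbalance on average. The shifts in the table are conditional on an extreme imbalance having occurred.
- A reader might infer that omitting age is why power falls short of 80%. It is not. The planned sample size relies on no covariate gain, and the 77% reflects the rounding of the effect size. It also assumes no gain from the planned baseline covariate and the full 17% loss, whereas the Sample size section expects loss to be small.

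**Conclusion.** The point holds as an optional efficiency improvement. As stated in the article, the primary model is a standard and valid analysis, but it makes no use of a baseline variable that is known for every child and may be prognostic across a 0 to 17 year range. On an assumed R² of 0 to 0.15 after baseline HbA1c, the gain is between nothing and about six percentage points of power (77% to 77–84% at 100 per arm on the unrounded inputs). The protection against an extreme chance age imbalance is worth up to about 0.14 HbA1c points. The size depends entirely on that assumption, since the documents give no figure for the relation between age and HbA1c.

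**What to change.** Unless the full protocol or analysis plan already does so, add age at diagnosis as a further pre-specified covariate in the primary ANCOVA, keeping baseline HbA1c and the correction for clustering within clinic. Fix the functional form before outcome data are seen. Linear, or linear plus quadratic, are both defensible, and the documents favour neither.

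The cost is one line of analysis wording and no new data. If age proves unrelated to the outcome, the loss is one or two degrees of freedom out of about 190.

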#### Qualitative Analysis

Qualitative data analysis is an on-going rather than discrete activity. Data from the qualitative interviews undertaken with a subgroup of children older than 8 years of age and parents will be subject to thematic analysis, which comprises a number of steps: 1) interviews will be audio-recorded and transcribed verbatim, 2) patterns of experience will be listed, which may arise from direct quotes or the paraphrasing of common ideas, 3) data relating to the already classified patterns will be identified, 4) related patterns will be combined and catalogued into sub-themes, and 5) themes will be developed. Themes that emerge from participants' accounts will be coded and subsequently collated to form a comprehensive picture of their collective experience. It is anticipated that this will provide a detailed, in-depth insight into the thoughts and experiences of the participants. Data will be explored to allow identification and comparison of similarities and differences between cases and between the two arms of the study. The analytical process will be undertaken in a way that ensures that the integrity of the original document is kept intact.

#### Cost Effectiveness Analysis

A cost effectiveness analysis will assess direct (management at diagnosis) and indirect (subsequent) health service costs against the primary outcome (HBa1C). All NHS resource use, including inpatient admissions, insulin use, contacts with the diabetes team, investigations, attendances at accident and emergency departments, ambulance journeys, contacts with general practitioners and other health professionals will be monitored prospectively and valued by standard methods [19] using national unit costs supplemented where necessary by cost information from participating centres. Non-NHS costs such as parental time off work and travel are also being assessed but will be reported separately. Cost effectiveness results will be reported in the form of an incremental cost effectiveness ratio unless either form of patient management dominates (lower cost with greater effect). A series of one-way sensitivity analyses will test the sensitivity of the conclusions to changes in the main base case assumptions used.

Given the multiple objectives of a management at diagnosis service for children and the consequent importance of the secondary outcomes in this study (psychological adjustment, coping, adaptation to diagnosis), a costs-consequences analysis will also be undertaken.

## Discussion

The primary objective of this research is to determine whether there are significantly different outcomes for children with newly diagnosed type 1 diabetes who are clinically well, when they are either admitted to hospital or managed at home for initiation of insulin treatment and education of child and family.

This trial poses various challenges, one of which concerns the recruitment of patients. Recruitment takes place almost concurrently with the diagnosis and parents and children may find it difficult to think about participating in a study at this distressing time. It will be down to the skill and expertise of the DECIDE project nurses, and members of the multi-disciplinary paediatric diabetes teams, to explain the trial to potential participants, to maximise recruitment.

Another challenge of the trial is that many participating centres may not have had any previous experience of providing home management. This has necessitated the development of a dedicated DECIDE manual to assist centres through the process. This outlines for the first time, the minimum requirements of safe, home-based care from diagnosis which could be equally deliverable in a variety of differing clinical services.

This will be the first RCT to evaluate the difference, if any, in terms of clinical and psychological outcomes of patients managed from diagnosis in the differing settings. It is anticipated that outcomes from this trial will provide evidence to inform national and international guidelines (e.g. NICE, ISPAD) concerning how best to initially manage children diagnosed with type 1 diabetes.
